## Description

The over-arching goal of this research is to test the effectiveness of a Mobile Recovery

- 1 Outreach Team (MROT) intervention for opioid overdose and/or opioid use disorder patients treated in Nevada's Emergency Departments (EDs). MROT's will provide peer coaching and mentorship, referrals to medication-assisted treatment (MAT), and opioid overdose education and naloxone as part of the State's SAMHSA STR Program. We will accomplish the research goal through the following two aims: (1) Determine the effectiveness of the MROT on (a) subsequent overdose, and (b) MAT uptake among patients presenting to a hospital ED for opioid overdose, and (2) Evaluate the MROT implementation and fidelity through comprehensive process evaluation. In addition, the research will examine the feasibility and acceptability of a mobile team intervention model in rural Nevada. Because we know Nevada has a unique landscape with many cities located in rural/frontier areas where a traditional model may not be feasible, we will expand our feasibility/acceptability research and outcomes evaluation to include examining the impact of alternative models in hospitals in the rural/frontier regions of Nevada.

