## Sampling Plan

- 4 Single state agency databases – Patient data from 3 databases maintained by the Nevada Department of Public and Behavioral Health will be linked at the state level, de-identified, and sent to the research team for quantitative analysis. The databases include: statewide hospitalization data, statewide mortality data, and statewide medication assisted treatment participant data, In person interviews with patients conducted after exposure to mobile outreach teams will be conducted by research assistants to assess team interaction,

demographics, and drug use behaviors and impact of the intervention on patients. In person interviews for feasibility and acceptability will be conducted in rural Nevada with emergency department staff and other applicable community members that may be utilized for mobile recovery activities.

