### Measured Variables

- 5 Intervention vs. Standard of Care: The exposure of interest is whether patients receive the MROT program or standard of care. Standard of care will be defined as receiving standard discharge instructions and a passive referral to local services. There are 2 primary outcomes

of interest that will be observed in the 9 months following the patient's initial contact with the MROT: MAT treatment initiation, and non-fatal overdose. Secondary outcomes of interest include MAT treatment retention and fatal overdose. All outcome variables will be measured using data that are available within the SSA databases and which will be provided to the research team in a linked, de-identified data set. Non-fatal overdose will be defined as experiencing an overdose that is treated by ED personnel in the six months subsequent to the initial contact with the MROT. In 2017 Nevada passed AB474, new opioid-related legislation that classified opioid overdose as a reportable condition. This law took effect July 1, 2017 and requires that ED clinicians make a name-based report to the public health authority when they treat an opioid overdose. This mandate should ensure that opioid overdoses are identified in the state surveillance databases. MAT treatment uptake will be measured in three ways. We will obtain records from the SSA that contain information about all patients enrolled in MAT through a state-funded or state-certified provider. First, to measure treatment uptake we will define a dichotomous variable representing whether patients enrolled in a MAT program. Second, we will define "time to treatment" as the time elapsed between the index overdose and enrollment in the MAT program. Third, we will follow MAT patients for 9 months and determine the duration of treatment participation for enrolled patients. Fatal overdose will be defined as a death of a patient that is determined to be opioid related (ICD-10 codes X42, X44, Y12, Y14, T40.0 – T40.6), as reported in the electronic death registry system. We will include all intentional, unintentional, and undetermined deaths in the initial analysis, and will conduct sub-analyses in which only unintentional and undetermined deaths are included.

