## Analysis Plan

- 6 We hypothesize that in the 9 months following their index overdose, patients exposed to the MROT will: H1: be more likely to initiate MAT (Primary outcome) H2: have fewer non-fatal ODs (Primary outcome) H3: be retained in MAT longer (Secondary outcome) H4: be less likely to die of a subsequent OD (Secondary outcome) All analyses will be conducted using the intent-to-treat principle. Demographic and descriptive statistics will be calculated at baseline and at 9-months following the index overdose. The baseline characteristics and main outcomes between the intervention and control groups will be compared using the chi-square test and the two-sample t-test. To test the hypotheses with the dichotomous outcome (initiation of MAT) and the ordinal outcome (incidence of non-fatal OD) we will use generalized linear mixed effects models (SAS PROC GLIMMIX) and Bayesian hierarchical models (SAS PROC MCMC) to account for the complexity of non-normal outcomes and intricate cluster effects due to the interdependence of patients within hospitals. The sensitivity analysis for Bayesian hierarchical models will also be performed. For the time to treatment, retention in treatment, and death due to subsequent OD outcomes, we will apply marginal Cox models (SAS PROC PHREG) to estimate the main effect of intervention exposure and use the robust sandwich covariance matrix estimation approach to account for the intracluster dependence. Individual demographic information including age, race, sex, drug of choice (heroin vs. prescription opioids), insurance type (e.g., Medicaid vs. private), and location of residence (urban vs. rural) will be included in the mixed effects models and marginal Cox models to control for potential confounding effects. We will obtain records from the SSA for 9 months prior to the index overdose for all participants, to allow us to control for prior history of non-fatal overdose and MAT utilization. Other covariates at the hospital level will include location (e.g., Northern Nevada vs. Southern Nevada, rural vs. urban) and hospital type (e.g., regional, university, trauma center, etc.). In addition to the statistical approach described above, we will also employ a propensity score (PS) matching approach as a secondary analysis. PS matching is particularly well-suited to "natural experiments" in which assignment to condition cannot be manipulated, such as the implementation of state programs. The approach involves calculating the probability of assignment to a treatment or exposure using logistic regression in which we enter observed characteristics that could influence assignment. In this case, known characteristics of patients such as age, sex, location of residence (rural vs. urban), previous history of overdose, or previous history of MAT enrollment. The PS reduces the large set of possible covariates that could influence selection into the intervention or control

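### H1 claims MAT initiation in general, but MAT is counted only at state-funded or state-certified providers, and the share counted may differ between MROT and control patients

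*Protocol*

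**What the plan says.** The Analysis Plan (section 6) sets the first primary hypothesis for patients exposed to the MROT: "H1: be more likely to initiate MAT (Primary outcome". The Hypotheses section (section 2) words it equally broadly.

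Measured Variables (section 5) fixes how this is observed. "All outcome variables will be measured using data that are available within the SSA databases", and the MAT records contain "information about all patients enrolled in MAT through a state-funded or state-certified provider". For uptake, "we will define a dichotomous variable representing whether patients enrolled in a MAT program". Time to treatment and duration of treatment come from the same records, as does the nine-month history of MAT used as a covariate.

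The Sampling Plan (section 4) describes the source more broadly, as "statewide medication assisted treatment participant data". The protocol does not say whether the two descriptions cover the same providers.

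On the exposure, the Description (section 1) says that the MROT provides "referrals to medication-assisted treatment (MAT), and opioid overdose education and naloxone as part of the State's SAMHSA STR Program". For controls, "Standard of care will be defined as receiving standard discharge instructions and a passive referral to local services".

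**The concern.** There are two linked problems.

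1. **The outcome measured is narrower than the outcome claimed.** A patient who starts MAT with a provider outside the state-funded or state-certified set is recorded as not having started. H1 and its conclusion carry no such limit.
2. **The exposure is itself a referral pathway.** The MROT refers within a state programme, and the outcome file is the state's record of the providers it funds or certifies. If MROT referrals go mainly to those providers, while control patients who find treatment use a wider mix, a larger share of true MAT is recorded under MROT. A programme that only changed where patients were treated could then look as if it had raised access to treatment.

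The planned adjustment and propensity matching deal with who is exposed. They do not deal with whether an outcome is recorded once a patient is exposed. For overdose, section 5 supports ascertainment by citing a statutory reporting duty. It offers nothing comparable for MAT.

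**Working it through.** **Inputs from the protocol.** Anticipated MAT access is 5% in controls and 33% under intervention (section 4.1). The conservative sample is 308 intervention and 521 control patients, with alpha 0.05 (section 4.2). Tests are two-sided (section 6.1). The protocol gives no capture proportions, so those below are assumptions.

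**The plan's own figures.** 33% vs 5% is a risk ratio (RR) of 0.33/0.05 = 6.6 and a difference of 28 points. With 308 vs 521 patients the power is above 99.9%. The stated power of at least 82% for effect size 0.2 returns as 82.1% for 829 patients with a chi-square effect size of 0.1 (equivalent to 0.2 with equal arms), and as 79.5% with the 308:521 split. That figure does not bear on this point.

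**Model.** Observed rate = true rate × capture proportion in that group. Hence observed RR = true RR × (MROT capture / control capture).

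**If the true rates are 33% vs 5%:**

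| Capture MROT / control | Observed | RR | Difference (points) |
|---|---|---|---|
| 70% / 70% | 23.1% vs 3.5% | 6.6 | 19.6 |
| 50% / 50% | 16.5% vs 2.5% | 6.6 | 14.0 |
| 90% / 50% | 29.7% vs 2.5% | 11.9 | 27.2 |
| 70% / 90% (reversed) | 23.1% vs 4.5% | 5.1 | 18.6 |

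Equal capture leaves the RR unchanged and shrinks the difference. Unequal capture moves the RR in whichever direction the inequality runs.

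**If there is no true effect and MROT capture is 90%.** The spurious RR is 0.90/0.33 = 2.73, 0.90/0.50 = 1.80 or 0.90/0.70 = 1.29. With observed rates a (MROT) and b (control), the chance of a significant result favouring MROT is Φ[((a − b) − 1.96·SE0)/SE1], where SE0 uses the pooled rate and SE1 the separate rates.

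Example with a true 10% and control capture 50%:
- a = 0.09 and b = 0.05
- pooled rate = (308×0.09 + 521×0.05)/829 = 0.0649
- SE0 = 0.0177 and SE1 = 0.0189
- (0.04 − 1.96×0.0177)/0.0189 = 0.28, and Φ(0.28) = 0.61

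| Control capture | RR | True 5% | True 10% |
|---|---|---|---|
| 33% | 2.73 | 67% | 92% |
| 50% | 1.80 | 36% | 61% |
| 70% | 1.29 | 12% | 19% |

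With equal capture the figure is the nominal 2.5%. With capture reversed (70% MROT, 90% control) the spurious RR is 0.70/0.90 = 0.78, against MROT. Clustering is ignored. With an illustrative design effect of 2, the 61% and 19% at a true 10% fall to 37% and 12%.

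**Tipping point.** The effect disappears when control capture / MROT capture = 1 / observed RR. If 33% vs 5% is observed, that ratio is 1/6.6 = 0.15, and with 90% MROT capture the control capture would be 0.90/6.6 = 14%. If the observed RR were only 1.5 or 2, the corresponding control capture would be 0.90/1.5 = 60% or 0.90/2 = 45%.

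**Effect size short of the tipping point.** If 33% vs 5% is what is recorded and capture is 90% / 50%, the true rates are 36.7% vs 10%, RR 3.7.

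**The case against.** A reader might infer that the primary effect is biased towards MROT. The protocol does not show this. It does not say where the MROT refers patients, that the local services offered to controls lie outside the counted set, or how much MAT lies outside it. State certification may cover most MAT programmes, and the Sampling Plan's description of the source points that way. MROT patients' treatment elsewhere is missed too. All of this stands, and it is why the point is a risk and not a demonstrated bias.

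A reader might also take the covariate "insurance type (e.g., Medicaid vs. private" as evidence that patients outside the counted providers are expected. Insurance describes the payer and certification describes the provider, so a privately insured patient can attend a certified programme. Adjusting for insurance could also absorb any capture gap that arises only through payer mix. It would not absorb a gap created by the referral itself.

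Nor does the gap carry over unchanged to every MAT variable. Retention is measured among patients already enrolled with a counted provider, so missed initiations do not produce the same bias there. Prior MAT precedes exposure, so MROT referral cannot make its capture differ.

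The false-positive figures rest on assumed capture. A 6.6-fold capture ratio would be needed to explain away the anticipated result, against 2.7-fold in the most extreme case tabulated. That stands for a result as large as the one anticipated, and much less for an RR of 1.5 to 2.

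Finally, a quantitative bias analysis is commonly left to a SAP, so its absence here is not an error in itself. The mismatch between the hypothesis and the outcome definition is in the protocol's own text.

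**Conclusion.** The point holds as a mismatch and a risk. The MAT outcome as defined is enrolment with a state-funded or state-certified provider, and H1 claims more than that. Because the intervention is a referral within a state programme, capture may differ by group in a way that the planned adjustment and matching are not designed to address. The likely direction favours MROT, on the inference that MROT referrals go to counted providers more often than control patients do. The protocol neither confirms nor excludes this.

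The size is unknown. It ranges from no distortion of the RR with equal capture (and an understated risk difference) to a spurious RR of 1.3 to 2.7 under the assumed 90% vs 70% to 33%. Capture alone is unlikely to produce a result as large as 33% vs 5%, but it could account for a modest one and could distort the size of any. The false-positive rates are illustrative. They depend on the assumed capture and true rates, and on ignoring clustering.

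**What to change.** 1. In sections 2, 5 and 6, restate H1, time to treatment and the retention hypothesis as MAT at a state-funded or state-certified provider, and limit the conclusions to that.
2. State what share or kinds of MAT provider the database covers, reconcile this with the broader description in the Sampling Plan, and state which providers MROT referrals go to.
3. Add a sensitivity analysis of H1 over group-specific capture rates, including equal and reversed cases. Report the control-to-MROT capture ratio at which the effect disappears (about 0.15 if 33% vs 5% is observed). If a SAP already contains this, a cross-reference is enough.
4. Treat any analysis by insurance type as exploratory. The protocol does not show that capture is more complete, or more alike between groups, for any payer.

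The sensitivity analysis uses data already in the linked set. The cost is a narrower claim, some documentation from the state partners and a little more analysis.

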#### 4.1 Sample Size:

In 2017, the six participating hospitals reported a total of 308 opioid-related poisoning visits to the ED, representing 37% (308/829) of the total visits statewide. Those numbers are highly conservative, because they are restricted to a small set of ICD-10 billing codes (primary diagnosis of T40.0, T40.1, T40.2, T40.3, T40.4, and T40.6). Other research found that using only ICD-9/10 billing codes related to opioid poisoning results in low sensitivity (as low as 25%). Additionally, rates of opioid-related visits have increased significantly over the past several years in Nevada (+12% 2010-2015, and +22% 2014-2015). Therefore, we anticipate that the actual number of intervention participants will be significantly higher. Using the findings from the sensitivity analysis above, we estimate the possible number of opioid-related poisonings for the 6 intervention hospitals to be 1232. The upper bound of the possible number of participants is represented by the total set of opioid-related ED encounters, which was 2635 in the six intervention hospitals in 2017, representing 37% (2635/7125) of encounters statewide. We anticipate 5% of control patients will access MAT compared to 33% of intervention patients. We anticipate that 7-12% of control patients will experience a non-fatal overdose in the 9 months following their index overdose, and that will be reduced by around 47% among intervention participants. According to unpublished data from the SSA, we anticipate 10% of control participants will die of an overdose in the next year compared to 5% in intervention participants.

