#### 4.2 Sample Size Rationale:

The alpha significance level of the power analysis is set to 0.05. At least 82% power will be achieved to detect a small effect size of 0.2 under the anticipated conservative sample size. Under different assumptions of effect size, such as medium effect size of 0.5 and large effect size of 0.8, our analysis strategy will have at least 99% power. For reasonably anticipated sample size 3316 (1232 intervention and 2084 control), at least 99% power will be achieved to detect as small as 0.1 effect size. Therefore, a very conservative sample of 829 (308 intervention and 521 control) patients will be sufficient to evaluate the primary outcomes. R package pwr was used for power analysis. To be our best knowledge, very few existing power analysis approaches can be applied to hierarchical models. In addition to the primary aims of the proposal, data will be used to develop a statistically reliable and computationally efficient power analysis procedure for hierarchical models and implement the proposed approach in an R package and a SAS macro.

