#### 6.1 Inference Criteria:

A p-value of  $<0.05$  will be considered statistically significant. 95% Confidence Intervals will be reported and all hypothesis testing will be two-sided. All analyses will be performed using SAS Version 9.4 for Windows.

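### The fatal overdose code list does not match the plan's own text: it takes in T40.5, and its external-cause codes cover no intentional deaths

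*Protocol*

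**What the plan says.** The protocol's Measured Variables section states the outcome in words: "Fatal overdose will be defined as a death of a patient that is determined to be opioid related". It then gives the codes in parentheses: "ICD-10 codes X42, X44, Y12, Y14, T40.0 – T40.6". On intent it continues: "We will include all intentional, unintentional, and undetermined deaths in the initial analysis", and adds that the investigators "will conduct sub-analyses in which only unintentional and undetermined deaths are included".

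Section 4.1 (Sample Size) counts opioid poisoning visits to the ED with a list written out code by code: "primary diagnosis of T40.0, T40.1, T40.2, T40.3, T40.4, and T40.6". That list passes over T40.5.

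The Analysis Plan makes death from a subsequent overdose a secondary outcome (H4), to be analysed with a marginal Cox model. The protocol does not explain any code. It also does not say whether a death needs an X or Y code together with a T40 code, or whether one listed code is enough.

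**The concern.** The list should deliver opioid-related deaths of every intent, and then allow the intentional ones to be set aside in a sub-analysis. As written it appears to do neither cleanly. One T40 code in the range is not an opioid code, and the codes that carry intent match the sub-analysis rather than the initial analysis.

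The stake is the set of deaths counted for H4. Missing deaths cost events and power. Deaths that the intervention is not aimed at would, if unaffected by it, pull the estimated effect towards no difference. A sub-analysis that selects the same deaths as the initial analysis says nothing about intent. The Sampling Plan has the state link and de-identify the data before sending them to the researchers, so deaths left out of the extract may be hard to recover later.

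**Working it through.** The plan states no figure that depends on this list, so the check is a comparison of code sets, followed by an illustration of scale.

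**Step 1. The T40 codes.**
- Measured Variables, range written out: {T40.0, T40.1, T40.2, T40.3, T40.4, T40.5, T40.6}.
- Section 4.1 list: {T40.0, T40.1, T40.2, T40.3, T40.4, T40.6}.
- The first set minus the second is {T40.5}. The second minus the first is empty.

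The documents alone show this mismatch. That T40.5 denotes cocaine comes from ICD-10, the classification the protocol names.

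**Step 2. The intent codes.** In ICD-10, X42 and X44 are accidental poisoning, and Y12 and Y14 are poisoning of undetermined intent. The intentional self-poisoning counterparts, X62 and X64, are not listed.

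| Intent | External-cause codes listed | Promised in initial analysis | Promised in sub-analysis |
|---|---|---|---|
| Unintentional | X42, X44 | yes | yes |
| Undetermined | Y12, Y14 | yes | yes |
| Intentional | none | yes | no |

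**Step 3. The two ways to read the list.**

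| | An X or Y code is required, with T40 naming the drug | Any one listed code suffices |
|---|---|---|
| Intentional opioid deaths | lost | can enter through a T40 code |
| Sub-analysis against initial analysis | same deaths | can differ |
| X44 or Y14 deaths with no opioid code | not counted | counted |
| Deaths whose only T40 code is T40.5 | counted if a listed X or Y code is present | counted |

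Neither column gives the outcome described in words. The T40.5 problem is in both columns; the other faults belong to one column each.

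**Step 4. Scale, as illustration only.** Inputs:
- Death rates from Section 4.1: "we anticipate 10% of control participants will die of an overdose in the next year compared to 5% in intervention participants".
- Sample from Section 4.2: "a very conservative sample of 829 (308 intervention and 521 control) patients".
- Two-sided testing at 0.05 (Section 6.1). Clustering is ignored.

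Power = Φ[(p₁ − p₂ − 1.96·SE₀)/SE₁], with SE₀ from the pooled rate and SE₁ from the separate rates.

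For 10% against 5%:
- Pooled rate = (521×0.10 + 308×0.05)/829 = 0.0814.
- SE₀ = √[0.0814×0.9186×(1/521 + 1/308)] = 0.0197.
- SE₁ = √[0.09/521 + 0.0475/308] = 0.0181.
- Power = 73.7%.

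The next rows rest on assumed shares, because the documents give none.

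| Assumption | Risk ratio | Power |
|---|---|---|
| List as intended | 0.05/0.10 = 0.50 | 73.7% |
| 5% of deaths missed in both groups | 0.50 | 71.2% |
| 10% missed in both groups | 0.50 | 68.5% |
| 20% missed in both groups | 0.50 | 62.6% |
| Non-opioid deaths add 1 point to each group | 0.06/0.11 = 0.55 | 68.7% |
| Non-opioid deaths add 2 points to each group | 0.07/0.12 = 0.58 | 64.3% |

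The missed-death rows belong to the first reading. The added-death rows belong mainly to the second. They should not be combined.

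**The case against.** The strongest reply is that the wording governs and the codes only illustrate it. The definition asks for a death determined to be opioid related, and the following sentence expressly includes intentional deaths, so the intention is clear. On this view the combination rule is coding detail for a statistical analysis plan that is not shown, and the meanings of the codes come from outside the protocol. The Section 4.1 list also served another purpose, a 2017 count of ED visits by primary diagnosis.

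Part of this stands. The absence of an and/or rule would not be a finding by itself. The Section 4.1 list is not an outcome definition. Deaths missed equally in both groups cost power but do not by themselves bias the ratio.

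The core remains. The protocol did not leave the codes to a later document; it fixed them, and they disagree with the adjacent sentence on intent and with its own opioid list. The code meanings are those of the classification it invokes.

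A reader might infer three stronger things, which the documents do not support:
- **That the list cannot capture intentional deaths and the sub-analysis must repeat the initial analysis.** This holds only if an X or Y code is required. Under the other reading, intentional deaths can enter through T40.
- **That deaths are both lost by intent and diluted through X44 and Y14.** These need opposite readings of the same list.
- **That the effect on H4 would shrink by a known amount.** With an assumed non-opioid share f of control deaths, unaffected by the intervention, the ratio is 0.5(1 − f) + f, or 0.55 to 0.65 for f from 0.1 to 0.3. Nothing in the documents supports such a share, and the 10% and 5% rates are for death from an overdose within a year, not worded as opioid-only.

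**Conclusion.** The concern holds as an internal mismatch. The T40 range includes a code that the plan's own opioid list omits, and the listed external-cause codes leave out an intent that the plan says it will include. Whichever way the list is read, it does not yield the opioid-related, all-intent set of deaths described in words.

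The size is unknown. The power and ratio figures above show what assumed shares would do; they do not estimate what will happen. The conclusion rests on the standard ICD-10 meanings of X42, X44, Y12, Y14 and T40.5, except for the T40.5 set difference, which needs only the protocol. Only secondary outcome H4 is affected: neither primary outcome is defined by this list. It should be corrected, but it does not threaten the main conclusions of the study.

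**What to change.** Before the mortality extract is requested, replace the list in Measured Variables with a rule that has two required parts:
- an external cause of X42, X44, X62, X64, Y12 or Y14; **and**
- at least one of T40.0, T40.1, T40.2, T40.3, T40.4 or T40.6, with T40.5 dropped.

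State that the initial analysis uses the full rule and that the sub-analysis excludes X62 and X64. The opioid codes then agree with Section 4.1, and the two analyses are defined by different intent codes.

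The cost is a short edit to the protocol and to the data request. No patient or site is affected, provided it is done before extraction.
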